## Appendix 1: Online Questionnaire

2. What sex were you assigned at birth?

- ☐ intersex / ambiguous  
☐ female  
☐ male

3. How do you define your gender identity? (tick as many as apply)

- ☐ man  
☐ trans man (female to male)  
☐ trans woman (male to female)  
☐ woman  
☐ non-binary gender (Third gender, Hijra)

4. How do you afford your hormones therapy or sex affirmation surgeries? (tick as many as apply)

- ☐ does not apply to me  
☐ most of it is covered by the medical scheme of my country  
☐ my private health insurance covers most of it  
☐ from my own pocket  
☐ I'm working extra hours to afford it  
☐ I'm doing sex work to afford it  
☐ I regularly sacrifice a meal to pay for it  
☐ I can't afford it  
☐ I don't need / don't want hormones or sex affirmation surgery for the time being  
☐ it is illegal in my country  
☐ other

5. How masculine or feminine are you perceived to be by those around you?

- ☐ very masculine  
☐ masculine  
☐ neither masculine or feminine  
☐ feminine  
☐ very feminine

exit

An exit button is always available at the beginning of each module. Respondent can always scroll back to it

6. What country do you currently live in? Drop down menu
7. Which of the following best reflects why you live in this country: (tick as many as apply)
- ☐ was born here, or my parents moved here
  - ☐ to study
  - ☐ to work
  - ☐ to follow a partner
  - ☐ to live more openly as gay/bi/lesbian/trans
  - ☐ to seek asylum
  - ☐ I came as a refugee
  - ☐ other
8. How old are you? Drop down menu
9. Would you say that you are open (out) as gay, lesbian, bisexual, or trans [answer 1 for not at all open (in) and answer 5 for open (out) to all or most people, you know], or answer some place in between]:
- ☐ 1 not at all open (*in*)
  - ☐ 2
  - ☐ 3
  - ☐ 4
  - ☐ 5 open (out) to all or most people I know
10. In general, would you say that your health is
- ☐ excellent
  - ☐ very good
  - ☐ good
  - ☐ fair
  - ☐ poor

*[Section on wellbeing and happiness (note: text in blue does not appear in the questionnaire)]*

11. On the whole, I am satisfied with myself.
- ☐ strongly agree
  - ☐ agree
  - ☐ disagree
  - ☐ strongly disagree
  - ☐ I don't know
12. How willing are you to take risks, in general?
- ☐ 10 very willing
  - ☐ 9
  - ☐ 8
  - ☐ 7
  - ☐ 6
  - ☐ 5
  - ☐ 4
  - ☐ 3
  - ☐ 2
  - ☐ 1
  - ☐ 0 very unwilling

*[single-item on time preference]*

13. I only act to satisfy immediate concerns, figuring that I will take care of future problems that may occur at a later date

- ☐ extremely characteristic of me
- ☐ somewhat characteristic of me
- ☐ uncertain
- ☐ somewhat uncharacteristic of me
- ☐ extremely uncharacteristic of me

**[sub-section: PHQ4]**

For the next four questions, think back over the last 2 weeks, how often have you been bothered by the following problems:

14. Feeling down, depressed or hopeless

- ☐ not at all
- ☐ several days
- ☐ more than half the days
- ☐ nearly every day

15. Little interest or pleasure in doing things

- ☐ not at all
- ☐ several days
- ☐ more than half the days
- ☐ nearly every day

16. Feeling nervous, anxious or on edge

- ☐ not at all
- ☐ several days
- ☐ more than half the days
- ☐ nearly every day

17. Not being able to stop or control worrying

- ☐ not at all
- ☐ several days
- ☐ more than half the days
- ☐ nearly every day

18. Imagine a ladder with steps representing happiness in life.

On which step of the ladder do you stand at this time? (*Answer 1 for worst possible life for me, answer 10 for best possible life, or choose a step in between that correspond to you*)

- ☐ 10 best possible life for me
- ☐ 9
- ☐ 8
- ☐ 7
- ☐ 6
- ☐ 5
- ☐ 4
- ☐ 3
- ☐ 2
- ☐ 1
- ☐ 0 worst possible life for me

*[Section on social support network]*

19. My family accepts me as I am

- ☐ strongly agree
- ☐ agree
- ☐ disagree
- ☐ strongly disagree
- ☐ I don't know

20. There is someone I can count on if things go wrong

- ☐ strongly agree
- ☐ agree
- ☐ disagree
- ☐ strongly disagree
- ☐ I don't know

21. There are people around me who like the same activities I do

- ☐ strongly agree
- ☐ agree
- ☐ disagree
- ☐ strongly disagree
- ☐ I don't know

22. There is someone who counts on me to lend a hand when they need it

- ☐ strongly agree
- ☐ agree
- ☐ disagree
- ☐ strongly disagree
- ☐ I don't know

*[Section on body appearance]*

23. I consider myself physically attractive

- ☐ strongly agree
- ☐ agree
- ☐ disagree
- ☐ strongly disagree
- ☐ I don't know

24. Most people would consider me good-looking

- ☐ strongly agree
- ☐ agree
- ☐ disagree
- ☐ strongly disagree
- ☐ I don't know

25. I think I am:

- ☐ very underweight
- ☐ somewhat underweight

- ☐ about normal weight
- ☐ somewhat overweight
- ☐ very overweight

*[Section on experience of homophobic reactions]*

26. Have you ever been **stared at or intimidated** because someone knew or presumed your sexual orientation or your gender identity? If yes, when was the last time?

- ☐ no, never
- ☐ yes, within the last 12 months
- ☐ yes, more than 12 months ago

27. Have you ever heard **verbal insults** directed at you because someone knew or presumed your sexual orientation or your gender identity? If yes, when was the last time?

- ☐ no, never
- ☐ yes, within the last 12 months
- ☐ yes, more than 12 months ago

28. Have you ever been **physically assaulted** because someone knew or presumed your sexual orientation or your gender identity? If yes, when was the last time?

- ☐ no, never
- ☐ yes, within the last 12 months
- ☐ yes, more than 12 months ago

*[sub-section on access to healthcare services]*

29. When did you last have an HIV test?

- ☐ within the last 6 months
- ☐ within the last 12 months
- ☐ more than 12 months ago
- ☐ never

30. In the last 12 months, have you avoided going to or delayed going to a health care facility for sexual health or for HIV-related services? (tick as many as apply)

- ☐ would be too risky for me
- ☐ I can't pay
- ☐ I'm embarrassed
- ☐ last time I felt stigmatised
- ☐ I'm worried someone may learn about my sexual orientation
- ☐ it's not convenient (transport, time, distance)
- ☐ I could not find the times
- ☐ it was not important to me
- ☐ I did not avoid or delay my health consultation
- ☐ other

31. Did you experience any of the following the last time you went to a health facility (tick as many as apply)

- ☐ I felt welcomed
- ☐ I had no negative experience

- ☐ verbal abuse (yelling, scolding, name calling, ...)
- ☐ physical abuse (pushing, hitting, physically hurt...)
- ☐ was given a condition (requirement) to change my sexual behaviour prior to treatment
- ☐ was given a condition (requirement) to change to change my gender identity prior to treatment
- ☐ refused to help me
- ☐ other

*[sub-section on stigma & discrimination at workplace]*

32. In the last 12 months, have you experienced any of the following at your current work or when you applied for a job? (tick as many as apply)

- ☐ I faced no discrimination
- ☐ my application was refused because I am gay, bi, lesbian, trans
- ☐ I was harassed or ridiculed at the workplace
- ☐ I was not promoted because I am gay, bi, lesbian, trans
- ☐ I was told not to show me being gay, bi, lesbian, trans
- ☐ I was denied certain work-related benefits because I am gay, bi, lesbian, trans
- ☐ I was told not to work with clients
- ☐ I'm not working
- ☐ I didn't apply because I'm gay, bi, lesbian, trans
- ☐ other

33. At work, do you earn less than your nearest heterosexual (straight) counterpart who does the same kind of work

- ☐ yes
- ☐ no
- ☐ don't know
- ☐ does not apply

*[Section on quality of sex]*

34. Over the past three months, how satisfied are you with the quality of your sexual life?

- ☐ 10 really satisfied
- ☐ 9
- ☐ 8
- ☐ 7
- ☐ 6
- ☐ 5
- ☐ 4
- ☐ 3
- ☐ 2
- ☐ 1 really not satisfied

35. I would like to have sex

- ☐ a lot more often
- ☐ a little more often
- ☐ I have enough sex as is
- ☐ a little less often
- ☐ a lot less often

*[Section on sociodemographic data]*

36. Your relationship situation

- ☐ single
- ☐ in a relationship with a man
- ☐ in a relation with a transgender person
- ☐ in a relationship with a woman
- ☐ both with a man and a woman
- ☐ I don't know

37. Education (highest degree completed):

- ☐ none
- ☐ primary school
- ☐ secondary /high school
- ☐ university first degree
- ☐ masters/doctorate

38. Current employment status:

- ☐ employed
- ☐ self-employed
- ☐ doing casual or part-time work
- ☐ unemployed
- ☐ student
- ☐ retired
- ☐ other

*[Section on economic situation]*

39. Which comes closest to your feelings about your income these days?

- ☐ living really comfortably on present income
- ☐ living comfortably on present income
- ☐ neither comfortable nor struggling on present income
- ☐ struggling on present income
- ☐ really struggling on present income

40. Considering all debts or loans of whatever type, were you behind with payments by more than 3 months at any time during the last 12 months?

- ☐ never
- ☐ rarely
- ☐ occasionally
- ☐ most of the time
- ☐ all the time
- ☐ does not apply

41. How often have there been times in your life when you have lived in poverty by the standards of that time?

- ☐ never
- ☐ rarely
- ☐ occasionally
- ☐ most of the time

*[Section on social situation]*

42. Think of a ladder representing where people stand in **your country**

At the **top** of the ladder are the people who are the **best off**. At the **bottom** are the people who are the **worst off**. Where would you place yourself on this ladder at this moment?

- ☐ 10 among those having most money, most education and

- most respected jobs
- ☐ 9
  - ☐ 8
  - ☐ 7
  - ☐ 6
  - ☐ 5
  - ☐ 4
  - ☐ 3
  - ☐ 2
  - ☐ 1 among those having the least money, least education and least respected jobs or no job

43. Now, think of a ladder representing where people stand in your **local community**

Where would you place yourself on this ladder at this moment?

- ☐ 10 highest social standing in my community
- ☐ 9
- ☐ 8
- ☐ 7
- ☐ 6
- ☐ 5
- ☐ 4
- ☐ 3
- ☐ 2
- ☐ 1 lowest social standing in my community

44. You would say you live in:

- ☐ a major city
- ☐ a medium- or small-size city
- ☐ a village
- ☐ a farm or an isolated house

45. People are different in their sexual attraction to other people. Which best describes your feelings? are you...

- ☐ attracted to other men or gay
- ☐ attracted to other women or lesbian
- ☐ attracted to both men and women or bisexual
- ☐ Straight or heterosexual
- ☐ I don't know

*Note: respondents answering 1 (gay), 3 (bisexual) or 5 (I don't know) will be offered to complete module 2*

*Respondents answering 2 (lesbian) or 4 (straight) will be redirected to question 61 (do you know your HIV status?)*

[ module 2 for gays, bisexuals, transgenders or men attracted to other men ]

exit

The following few questions are more specific for gay, bi, transgender and men attracted to other men

☐ OK *(click is required)*

An exit button is always available at the beginning of each module. Respondent can always scroll back to it

[Section on HIV prevention and exposure to HIV infection]

46. In the past 3 months, with how many **different** sexual partners did you have **anal sex without any kind of HIV prevention method**? That is without condoms, PrEP or an undetectable HIV viral load?
- ☐ 0
  - ☐ 1, steady
  - ☐ 1, casual
  - ☐ 2
  - ☐ 3 to 10
  - ☐ more than 10
  - ☐ Does not apply to me
47. Thinking about your last **anal sex partner without any kind of HIV prevention method** (that is without condom, PrEP or an undetectable viral load), how did it go?
- ☐ my partner fucked me (I was receptive)
  - ☐ I fucked him/her (I was insertive)
  - ☐ I both fucked and got fucked (I was both receptive and insertive)
  - ☐ does not apply to me
48. Thinking about your last **anal sex partner without any kind of HIV prevention method** (that is without condom, PrEP or an undetectable viral load), did you know his HIV status? tick as many as apply
- ☐ I didn't ask
  - ☐ s/he's HIV negative
  - ☐ s/he's HIV positive and I don't know his/her viral load
  - ☐ s/he's HIV positive AND undetectable
  - ☐ I was on PreP
  - ☐ s/he was on PreP
  - ☐ I don't remember
  - ☐ I had more than one partner and I do not know everyone's HIV status
  - ☐ does not apply to me

49. In the last 3 months, how much of the sex you've had with men has been under the influence of alcohol or any other drug?

- ☐ none of it
- ☐ almost none of it
- ☐ less than half
- ☐ about half
- ☐ more than half
- ☐ almost all of it
- ☐ all of it
- ☐ does not apply to me

50. In the past 3 months, did you share drug injecting equipment (needles, syringes) with someone else?

- ☐ yes, once
- ☐ yes, several times
- ☐ no, I don't share my equipment
- ☐ no, I don't inject drugs

51. What do you do if your potential date/sexual partner tells you they are is HIV positive? (tick as many as you like)

- ☐ I do not see them again
- ☐ I am not comfortable having sex with them
- ☐ I am comfortable having sex with them because we use a condom, I am on PrEP and/or he is undetectable
- ☐ I'm HIV positive too

52. In the last 12 months, how often have **you paid someone** to have sex with you?

- ☐ never
- ☐ 1-2
- ☐ 3-10
- ☐ 11-50
- ☐ more than 50 times

53. In the last 12 months, how often have **you been paid** to have sex

- ☐ never
- ☐ 1-2
- ☐ 3-10
- ☐ 11-50
- ☐ more than 50 times

54. I feel comfortable in gay bars

- ☐ 7 strongly agree
- ☐ 6
- ☐ 5
- ☐ 4 undecided
- ☐ 3
- ☐ 2
- ☐ 1 strongly disagree
- ☐ does not apply

55. Social situations with gay men make me feel uncomfortable

- ☐ 7 strongly agree

- ☐ 6
- ☐ 5
- ☐ 4 undecided
- ☐ 3
- ☐ 2
- ☐ 1 strongly disagree
- ☐ does not apply

56. I feel comfortable being seen in public with an obviously gay person

- ☐ 7 strongly agree
- ☐ 6
- ☐ 5
- ☐ 4 undecided
- ☐ 3
- ☐ 2
- ☐ 1 strongly disagree
- ☐ does not apply

57. I feel comfortable discussing homosexuality in a public situation

- ☐ 7 strongly agree
- ☐ 6
- ☐ 5
- ☐ 4 undecided
- ☐ 3
- ☐ 2
- ☐ 1 strongly disagree
- ☐ does not apply

58. I feel comfortable being sexually attracted to other men

- ☐ 7 strongly agree
- ☐ 6
- ☐ 5
- ☐ 4 undecided
- ☐ 3
- ☐ 2
- ☐ 1 strongly disagree
- ☐ does not apply

59. Homosexuality is morally acceptable to me

- ☐ 7 strongly agree
- ☐ 6
- ☐ 5
- ☐ 4 undecided
- ☐ 3
- ☐ 2
- ☐ 1 strongly disagree
- ☐ does not apply

60. Even if I could change my sexual orientation, I wouldn't

- ☐ 7 strongly agree

- ☐ 6
- ☐ 5
- ☐ 4 undecided
- ☐ 3
- ☐ 2
- ☐ 1 strongly disagree
- ☐ does not apply

61. Do you know your HIV status?

- ☐ I'm HIV-negative
- ☐ I'm HIV-positive
- ☐ I don't know
- ☐ I don't want to answer

- ☐ PREV (*clicking here brings the respondent to earlier module in case she/he would like to change*)
- ☐ DONE (*brings the respondent to a thank you message*)

*Note: participants that have answered "I'm HIV-positive" at question will be offered to participate to module 3 (see next page)*

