### *Timing and intervals between the survey rounds*

This is the first edition of the global LGBTI survey. Future annual edition of the survey will be determined after the evaluation of the 2019 edition. A tentative timeline for this survey can be found in appendix 3.

One interest of eventual annual editions of the survey is to study the changes and the evolution of key variables over time per country. The study does not track respondents year after year. It will analyse how indicators such as well-being, mental health, HIV self-prevention, homophobia for example are evolving following changes in LGBTI legislation, in government, or in the economy at country level.

This is similar as other surveillance. It typically does not include the same participants in repeat surveys. Ideally, behavioural surveys should be conducted at intervals in order to capture changes in risk behaviours and the HIV epidemic over time. This survey can therefore serve as a baseline for any future undertakings.

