### *Questionnaire development*

The questionnaire of the survey contains established instruments for collecting survey data among key populations, such as LGBTI people, using validated questions and scores. These instruments include questions that have been used throughout the world; thus, their continued use will enable researchers to compare survey results across countries. The standardized instruments provided with these guidelines were designed to be self-administered using electronic or web-based data collection methods.

The questionnaire was built on the following four principles:

1. The process must preserve the complete anonymity of respondents. The privacy and security of respondents must be ensured at every step of the survey;
2. Questionnaire should be as short as possible. Only questions that are necessary should be included;
3. Filling out the online questionnaire should expose participants to no more than minimal risk, such as minimal discomfort, minimal anxiety;
4. Questions selected should have their reliability and validity already demonstrated and their collection should enable triangulation with other surveys.

We followed the following **key steps in questionnaire development**:

- decided on methods for questionnaire administration;
- determined investigation topics (questionnaire domains);
- developed and adapted the questionnaire;
- conducted cognitive testing;
- pre-tested the questionnaire;
- pilot tested the survey tool.

The content of the questionnaire is harmonized with standard indicators and protocol checklists used in behavioural surveillance. The questionnaire is organised as modules focused on topics, such as:

- demographics
- time preference, risk aversion
- socioeconomic status, including a question on financing hormones for transgender people
- behaviours increasing vulnerability to HIV infection (e.g. unprotected receptive anal intercourse, buying sex, selling sex, sharing nonsterile injecting equipment, alcohol and drug use)
- stigma and discrimination in the community, at workplace and health facility (sexual orientation, gender identity, HIV)
- internalized homophobia
- violence
- general health status
- mental health, including depression
- social support network, including family
- HIV prevalence, access to HIV and other health services, HIV services uptake:
  - knowledge of serostatus
  - eligible but not on HIV treatment
  - viral load suppression
  - unsuppressed viral load
  - currently in care

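### Question 18 puts the worst possible life at 1 in its instruction and at 0 in its answer list, so scores of 0 and 1 may not mean the same thing for all respondents

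*Protocol*

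**What the plan says.** Question 18 (Protocol, Appendix 1) asks respondents to place themselves on a ladder of happiness in life. The instruction in the stem is "Answer 1 for worst possible life for me, answer 10 for best possible life", or a step in between. The answer list starts at "10 best possible life for me", goes down through unlabelled steps to an unlabelled 1, and ends at "0 worst possible life for me".

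The item closes the block on well-being and happiness. The section on timing and intervals between survey rounds names well-being among the indicators that eventual annual editions would follow by country: "It will analyse how indicators such as well-being, mental health, HIV self-prevention, homophobia for example are evolving". The section on questionnaire development says that the questionnaire contains established instruments, "using validated questions and scores". The section on languages and translations makes the English version the source for all translations, with back-translation by a second translator and resolution of discrepancies.

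**The concern.** The same description, the worst life imaginable for the respondent, is attached to two different numbers within one item. Someone in that state is directed to 1 by the instruction and to 0 by the label. Once the answer is stored, a 1 cannot be read with certainty: it may come from a person at the floor who followed the instruction, or from a person one step above the floor who followed the list. No later analysis rule can fully recover which was meant, because the anchor that a respondent used is not recorded.

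At stake is how the bottom of the well-being scale is read, and whether this survey can serve as a clean baseline for that item. If the wording were corrected only in a later edition, the use of the lowest scores could change between rounds for a reason unrelated to well-being.

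**Working it through.** **1. The two parts of question 18, side by side**

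| | Instruction | Answer list |
|---|---|---|
| Top anchor | 10 | 10 |
| Bottom anchor | 1 | 0 |
| Number of steps | 10 (1 to 10) | 11 (0 to 10) |
| Meaning of a score of 1 | worst possible life | unlabelled, one step above the worst |
| Meaning of a score of 0 | outside the stated range | worst possible life |

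Both parts are complete in the text, so the conflict is not caused by missing or broken extraction.

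**2. Comparison with the other numeric scales in Appendix 1**

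- Question 9 uses the same kind of instruction, "answer 1 for not at all open (in) and answer 5 for open (out) to all or most people", and its list runs from 1 to 5 with matching labels. No conflict.
- Question 12 has a list that ends at "0 very unwilling", and its stem gives no numeric anchor. No conflict.
- Questions 34, 42 and 43 have lists from 1 to 10; question 43, for example, ends at "1 lowest social standing in my community". No conflict.

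Only question 18 contradicts itself. The comparison does not show which anchor was intended: question 12 is a precedent for 0-10, and the two other ladders (42 and 43) are precedents for 1-10.

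**3. Possible size**

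The protocol gives no figure for this item, so there is none to reproduce. It gives neither the share of respondents at the floor nor the share who would follow the instruction. Both are assumed below.

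*Scenario A: only respondents at the floor are affected.*
Mean shift = share at floor × share of these who follow the instruction × 1 step.

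- 5% at the floor, half follow the instruction: 0.05 × 0.5 × 1 = 0.025
- 15% at the floor, half follow the instruction: 0.15 × 0.5 × 1 = 0.075

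That is about 0.03 to 0.08 points upward, relative to everyone using 0 as the floor.

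*Scenario B: those who follow the instruction compress the whole scale.* Suppose that a position x on the 0-10 scale is recorded, on average, as 1 + 0.9x. The individual shift is then (1 + 0.9x) − x = 1 − 0.1x: +1.0 at x = 0, +0.5 at x = 5, and 0 at x = 10. With an assumed mean of 5 and a share q who respond in this way, the mean shift is 0.5q:

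- q = 10%: 0.05
- q = 50%: 0.25
- q = 100%: 0.50

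Scenario B asks more of respondents, since they would have to ignore the visible 0 and rescale every step. In both scenarios the individual shift is largest at the bottom and vanishes at the top.

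**The case against.** The strongest case on the other side is that the contradiction is real but does little harm.

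- **The labelled 0 is visible.** A respondent at the floor sees a box that carries exactly the right description, while 1 has no label. Many may simply tick 0. This stands: the ambiguity is a risk whose extent is unknown, not a demonstrated misclassification.
- **No planned analysis is shown to depend on it.** Later annual editions are conditional on an evaluation of the 2019 one. The text on indicators over time speaks of well-being and does not name question 18; the same block also holds question 11 and the PHQ-4 items. Neither of the two first research questions names happiness, and the item plays no part in the sample-size rationale. This stands and keeps the point minor.
- **Unchanged wording would largely cancel within a country over time.** This is fair if the wording and the response habits stay the same. It does not help if the wording is corrected between rounds.

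A reader might infer more than the documents support, in four ways.

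- *That the share scoring 0 is halved.* That only restates the assumed even split. The protocol also defines no lowest-life category or cut-off for this item.
- *That translators will silently correct one anchor, so that the scale differs by language.* The back-translation step would tend to bring a changed digit to light.
- *That the conflict is certain to stand in every translation.* A faithful translation would carry it over, but the translated questionnaires are not shown. Both outcomes are reasons to check, not findings.
- *That 0 was plainly intended.* The documents do not settle this.

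**Conclusion.** The point holds as an inconsistency within one item. The instruction and the answer list of question 18 place the worst possible life at different scores, no passage says which governs, and scores of 0 and 1 may therefore not mean the same thing for all respondents.

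The size cannot be determined from the documents. With an assumed 5-15% at the floor and an assumed even split between anchors, the mean moves by about 0.03 to 0.08 points. A shift of 0.25 would need half of all respondents to rescale the whole ladder and a mean near 5, also assumed. The effect falls mainly on the lowest scores.

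Severity is minor: one single-item measure, outside the two first research questions. It is still worth correcting, because this is fixed wording put before respondents, and the ambiguity cannot be fully removed afterwards.

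**What to change.** Before launch, give the instruction and the answer list of question 18 the same bottom anchor, following the source instrument. There are two consistent versions:

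- change the instruction so that 0 is the worst possible life, a one-digit change that fits the existing 0-10 list; or
- drop the 0 option and attach the bottom label to 1, which gives a 1-10 ladder like those in questions 42 and 43.

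Then check the same line in every translation against the corrected English version. The cost is one digit or one answer option, plus one line to check per language. The section on data management places rollout after ethics clearance, so on the protocol's own timing the change can be made before any data exist.

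If data have already been collected with this wording, report the inconsistency with any result for this item and run a sensitivity analysis that combines scores 0 and 1. That removes the ambiguity at the floor at the price of one step of resolution. It would not undo a rescaling of the whole ladder as in scenario B. If a later edition uses corrected wording, state the change wherever rounds are compared.
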